### Qualitative evaluation

This study will conduct in-depth interviews among participants, maternal care provider, and hospital administrators. The research team will recruit participants for in-depth interviewees at the study site to explore the facilitating and hindering factors that influence the implementation of SDM.

The inclusion criteria for interviewees will be the same as those for the aforementioned focus group interviews, with the exception that expectant and new mothers should be participants in the intervention group. The exclusion criteria for interviewees will also be the same as those for the focus group interviews.

To protect the privacy of the participants, in-depth interviews are used instead of focus group interviews, as mothers may have prior experience with mental health services at this stage. This study aims to recruit a total of 30 mothers and 15 maternal care providers and hospital administrators in total. However, the recruitment will continue until data saturation is reached. The interviews will last between 0.5 and 1 h. For expectant and new mothers, the interviews will focus on the use of decision aids, as well as their experiences and perceptions related to SDM. For maternal care providers and hospital administrators, interviews will focus on perceived facilitators and barriers to SDM in maternal mental health services. The data analysis methods for the in-depth interviews are the same as those described previously for the focus group interviews.

## Discussion

Previous literature has documented the challenges of implementing SDM in the real-world settings. Some providers are concerned about the strength of evidence supporting decision aids, increased workloads associated with using them, and the lack of supportive environment [42]. Patients may find it challenging to comprehend the information presented in decision aids, and they may not want decision-making responsibility when facing difficult diagnoses [43]. To address the implementation challenges of incorporating a patient decision aid into clinical practice, this study aims to develop and evaluate an IP-SDM model for patients with PND in maternal care. The IP-SDM model will encompass a patient decision aid as its centerpiece, as well as multiple intervention components such as decision coaching and clinical consultation delivered by a multi-disciplinary team of providers. The proposed IP-SDM model will involve task shifting and sharing to alleviate the workload of providers. For instance, decision coaching will be conducted by nurses. Considering the limited time frame of maternal care consultations in China’s public hospitals, nurses may be better suited to communicate accurate and up-to-date evidence to patients and make decisions with patients based on their needs and preferences. Also, this study will adopt a participatory design approach to ensure that the patient decision aid can be understood by expectant and new mothers. The IP-SDM model may engage the family as well if the patient wants to share the decision-making responsibility with her family.

Furthermore, the IP-SDM model aims to increase acceptance of evidence-based mental health services for PND in maternal care settings. In these settings as well as other primary care settings, patients may not seek care for mental health concerns due to stigma or lack of mental health literacy [44]. Additionally, providers may lack the necessary skill sets or time to deliver mental health services [45]. Obstacles at the health system level may include a lack of political commitment, resources, guidelines, and health information systems to facilitate collaborative care [46–48]. To address these potential challenges, this study will develop a patient decision aid based on the best available evidence that can support both patients and providers in the decision-making process. In addition, with input from various stakeholders including hospital administrators, the IP-SDM care model will be integrated into the clinical practice to overcome potential organizational obstacles. Also, the cost-effectiveness of implementing the IP-SDM model will be evaluated to facilitate its future dissemination.

This study has several limitations. First, contamination can be a threat that biases the results towards null. Contamination is possible since it is not feasible to conduct a CRT design as discussed before. To identify the effects of SDM and alleviate the bias that may be introduced by contamination, this study will use randomization as the instrumental variable and examine how the assessed level of SDM after intervention would affect outcomes of interests. Second, the generalizability of this study should be interpreted with caution. The study site of this study was selected to ensure that mothers with mental health needs could access relevant services during the study. However, only a few maternal and child healthcare institutions in China have already integrated the screening and intervention for PND in routine maternal care. Thus, the findings may not be generalized to other regions of China. To maximize generalizability, this is an open-label trial with its interventions fully embedded into daily clinical practice.

Despite these limitations, this study will make the following contributions to the field. First, this study aims to contribute to our understanding of how SDM impacts mental health outcomes. This study will investigate not only how SDM affects mental health outcomes but also explore the potential mechanisms underlying such impacts, using causal mediation analysis. Second, this study will develop a culturally relevant and responsive IP-SDM model for the Chinese population. Most previous studies on SDM were conducted in high-incomes countries, with a lack of research on the Chinese population. Through a participatory design approach, the IP-SDM model will take into account the perspectives and cultural contexts of various stakeholders. For instance, the IP-SDM model will incorporate the input of family members in the decision-making process between patients and providers. Lastly, this study will explore an IP-SDM model to integrate mental health services into maternal care. The findings on the role of SDM in the diagnosis and treatment of PND could have important implications for other common mental disorders in the general population.

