### ③ Randomization and blinding

This study will use permuted block randomization to group the participating women, ensuring a balance across treatment groups. Although a cluster randomized trial (CRT) design would be preferred to avoid potential contamination, simple randomization will be adopted in this single-center study due to the following feasibility issues of conducting a CRT. First, obstetricians at the outpatient maternal care clinics are subject to frequent rotating shifts. Second, there are only several maternal care providers who have been trained to provide on-site mental health services, making them less than ideal targets for randomization and intervention as well.

Prior to recruitment, a non-participating third-party statistician will generate random numbers and create a random assignment table. This table will assign each participant to a group (intervention or control) in a 1:1 ratio based on the order of enrollment. A member of the research team member, who is not involved in participant recruitment, will assign each participant a number in order according to the random assignment table. The assigned number will be placed in a sealed and opaque envelope. During the trial, randomization will take place after a participant has completed informed consent. At the time of opening the envelope, two members of the research team must be present, and the name of the participant with the envelope numbers will be recorded.

Because the intervention group will receive the patient decision aid, and providers will be required to intervene with this group, it will not be possible to blind the mothers and providers. To minimize bias, during the baseline and follow-up assessments, the raters will be blinded to the group assignment.

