### ④ Sample size

The primary outcome indicator in this study is the level of decisional conflict at one month after baseline, which is a continuous variable. For the comparison of continuous variable outcome indicators in randomized clinical trials, the sample size can be estimated by the following equation.

Sample size of each group:

$$n = \frac{{2 \times {{({z_{(1 - \alpha /2)}} + {z_\beta })}^2}}}{{{{(\frac{\Delta }{\sigma })}^2}}}$$

Among them, α is set to 0.05, the Z_(1−α/2)_ takes the value of 1.96, while β is set to 0.80, and Z_β_ takes the value of 0.84. ∆/σ is the effect value and is set to 0.3 with reference to previous literature [37], resulting in a required sample size of 174 participants per group. Considering that some of the study participants (assumed to be ≤ 15%) might drop out of the study, the total target of recruiting participants is set at 410 after appropriate expansion of the sample size, and the intervention and control groups are assigned in a 1:1 ratio.

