**Patient Decision Aid**: Participants in the intervention group will receive a patient decision aid for PND prior to their clinical consultation. The patient decision aid will be distributed as a paper booklet, similar in size to the educational materials on perinatal mental health that are routinely distributed at the study site. The patient decision aid will support patients to identify their decision-making problems, understand treatment alternatives, and support them to discuss PND screening results and treatment options with maternal care and mental health professionals, and facilitate SDM.**Decision Coaching**: One week after the clinical consultation, the mother will receive a telephone call back from the mental health nurse, during which the nurse will counsel the patient on decision making based on the IP-SDM model. Specific components include identifying decision problems, exchanging evidence-based information, clarifying the patient’s values and preferences, assessing the feasibility of possible treatment modalities, and evaluating preferred options with the patient. The nurse’s decision coaching will also be available to family members if the patient agrees and requires it.**Clinical Consultation**: If patients attend the study site’s mental health clinic and the joint psychological specialist clinic, the clinician will also conduct a shared decision-making process with the attending pregnant and postpartum women, following the steps in the IP-SDM model. This process will also engage the family if the patient agrees and requires it.

Mental health nurses at the study site, as well as physicians in the mental health clinic and joint psychiatric specialist clinic, will receive training on the implementation of the IP-SDM model, including how to use decision aids with patients and how to provide decision support to patients in decision coaching and clinical consultation. In addition to the training, the research team will develop communication scripts prepared in a step-by-step decision-making process to help health care providers deliver standardized interventions and thereby prevent “contamination” of interventions.

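### The sample size makes no stated allowance for the contamination the protocol acknowledges; unless 0.3 SD is already net of it, the primary test falls short of 80% power when dropout reaches 15%

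*Protocol article*

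**What the plan says.** **Sample size (section ④).** The primary outcome is decisional conflict at one month. The standardised effect "is set to 0.3 with reference to previous literature". With a two-sided alpha of 0.05 and z values of 1.96 and 0.84, the section states the result as "resulting in a required sample size of 174 participants per group". Dropout of up to 15% is the only reason given for raising the total to 410.

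**Randomisation (section ③).** A cluster design is described as preferable for avoiding contamination but not feasible. One reason is that "there are only several maternal care providers who have been trained to provide on-site mental health services".

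**Intervention (section ⑤).** Mental health nurses and clinic physicians at the site are trained in the new model. Communication scripts are meant to "help health care providers deliver standardized interventions and thereby prevent" contamination.

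**Analysis (section ⑦).** Outcomes at a single time point, with decisional conflict at one month as the example, are compared by t-test under intention to treat. Section ⑥ lists decisional conflict among the baseline measures.

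**Discussion (limitations).** The protocol says that "contamination can be a threat that biases the results towards null", calls contamination possible, and proposes randomisation as an instrumental variable for the level of shared decision-making (SDM).

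**The concern.** The protocol names a bias towards the null that follows from randomising individuals, but sizes the trial without referring to it. The staff who deliver the new model also appear to serve controls. Usual care (section ①) includes discussion of treatment options and a call from a perinatal mental health nurse within a week, and section ⑤ names no separate staff for the control arm.

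Neither stated safeguard protects the power of the primary test. Scripts standardise what the intervention arm receives, but nothing described stops trained staff from using the same skills with controls. The instrumental-variable analysis addresses a different question, the effect of the SDM level. It draws on the same randomised contrast, so it does not restore power to the t-test.

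If contamination occurs and 0.3 SD did not allow for it, a real benefit is more likely to be missed than the plan states. A null result would then be hard to read as either an ineffective model or a diluted comparison.

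**Working it through.** **Inputs from section ④.** z = 1.96 (two-sided alpha 0.05), z = 0.84 (80% power), Δ/σ = 0.3, dropout up to 15%, allocation 1:1.

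**Step 1: the plan's own figures.**
- n = 2 × (1.96 + 0.84)² / 0.3² = 15.68 / 0.09 = 174.2, which the plan gives as 174.
- 174 / 0.85 = 204.7, so 205 per group and 410 in total.

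Both figures reproduce. Power at 174 per group and 0.3 SD is 79.9%. The whole increase from 174 to 205 is taken up by dropout, so nothing is left for contamination if dropout reaches 15%.

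**Step 2: unadjusted comparison with dilution.** Let c be the share of the effect lost to contamination, so the observed effect is d = 0.3 × (1 − c). The protocol gives no rate, so c is an assumption. Power ≈ Φ(d × √(n/2) − 1.96).

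For example, with c = 0.10 and n = 174: d = 0.27, 0.27 × √87 = 2.518, and Φ(0.558) = 0.712.

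| c (assumed) | d | 174 per group | 205 per group |
|---|---|---|---|
| 0 | 0.300 | 79.9% | 85.9% |
| 5% | 0.285 | 75.8% | 82.3% |
| 10% | 0.270 | 71.2% | 78.0% |
| 20% | 0.240 | 61.0% | 68.1% |
| 30% | 0.210 | 50.0% | 56.6% |

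With all 205 per group analysed, power stays at or above 80% up to c of about 7.8%. The exact t distribution changes these figures by at most about 0.3 percentage points.

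**Step 3: adjustment for baseline decisional conflict.** With correlation r between baseline and one-month scores, the effective standardised effect is d / √(1 − r²). The protocol gives no r, so 0.3 and 0.5 are assumptions.

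For example, with c = 0.10 and r = 0.5: 0.27 / √0.75 = 0.3118, 0.3118 × √87 = 2.908, and Φ(0.948) = 0.828.

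| c (assumed), 174 per group | unadjusted | r = 0.3 | r = 0.5 |
|---|---|---|---|
| 0 | 80% | 83% | 90% |
| 10% | 71% | 75% | 83% |
| 20% | 61% | 65% | 73% |

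**Step 4: what 0.3 SD would imply if it were net.** The undiluted effect would be 0.3 / 0.9 = 0.333 at 10% loss, or 0.3 / 0.8 = 0.375 at 20%. Section ④ makes no such statement.

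**The case against.** A reader might infer that the plan expects contamination and that its 80% power is therefore wrong. The document does not support this. It calls contamination possible and gives no rate. A power statement is conditional on the effect it names, and 80% for a between-arm difference of 0.3 SD is correct. The cited source is not at hand, so 0.3 SD may already be the contrast achievable at this site. In that case nothing is lost.

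Nor does 80% require zero contamination. Dropout of 15% is an upper bound, and with less dropout the trial can absorb a small dilution.

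Some handling already exists. The centrepiece of the model is a paper booklet given to intervention participants, which staff drift alone would not pass to controls. The one-month survey measures actual participation in decisions in both arms, so the main consequence of contamination through providers will be visible.

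All of this stands, and it makes the power loss conditional. It does not remove the gap: the protocol acknowledges a bias to the null, sizes the trial without mentioning it, and fixes an unadjusted test that leaves available precision unused. The assumed effect and the primary test are both stated in this document, so the point does not depend on a document that is not shown.

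**Conclusion.** The point holds in conditional form. Sections ③ and ④ and the Discussion do not fit together, because an acknowledged dilution has no counterpart in the sample size. If 0.3 SD is the effect without contamination and dropout reaches 15%, power is about 71% at 10% dilution and 61% at 20%. If all 205 per group are analysed, it is about 78% and 68%.

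The size of the loss rests on assumed dilution rates and on 0.3 SD being undiluted, neither of which the document settles. There is no arithmetic error in 174 or 410. This should be corrected, but it does not invalidate the design.

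**What to change.** 1. **Primary analysis (section ⑦).** Replace the unadjusted t-test of one-month decisional conflict with a linear model containing treatment group and baseline decisional conflict. The baseline score is already collected, so this needs no new data and no added recruitment. It recovers part of the loss but not all: at 20% dilution and 174 per group, power stays below 80% for both assumed correlations.

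2. **Sample size (section ④).** State whether 0.3 SD is net of contamination, with the reason. If it is not, give power over an assumed dilution range such as 10 to 30%. The cost is a less favourable stated power.

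3. **Optional: measure contamination.** In the one-month survey, ask both arms whether they saw the decision-aid booklet, and report the SDM level among controls, which is already measured. The cost is one yes/no question. Do not ask controls simply whether a nurse called them: usual care includes such a call, so the answer would count routine care as contamination.

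4. **Intervention (section ⑤).** Describe the scripts as standardising delivery, and drop the claim that this prevents contamination.

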## Data Availability

Data sharing is not applicable to this study protocol.

## Abbreviations

PND: Perinatal depression
SDM: Shared decision-making
IP-SDM: Interprofessional shared decision-making
RCT: Randomized controlled trial
SPIRIT: Standard Protocol Items:Recommendations for Interventional Trials
IPDAS: International Patient Decision Aids Standards
CTA: Cognitive task analysis
EPDS: Edinburgh Postnatal Depression Scale
OPTION: Observing Patient Involvement in Decision Making
MDT: Multidisciplinary team
CRT: Cluster randomized trial
TDABC: Time-driven activity-based costing
ICER: Incremental Cost-Effectiveness Ratio
